## Cohort Allocation

Volunteers will be randomized to one of six vaccine cohorts. Within each vaccine cohort, 2 volunteers will be randomized to receive placebo, and 10 volunteers to receive vaccine.

# Selection and Enrollment of Volunteers

## Inclusion Criteria

1. Males or females between 18 and 50 years, inclusive.
2. Good general health as a result of review of medical history and/or clinical tests at screening.
3. Available for the duration of the trial (78 weeks).
4. Willingness to participate in the study as evidenced by signing the informed consent document.

## Exclusion Criteria

1. Pregnancy as determined by a positive urine human chorionic gonadotrophin (ß-hCG), if female.
2. Volunteer unwilling to use reliable contraception methods for the duration of the trial, if female.

(Reliable methods of birth control include: pharmacologic contraceptives including oral, parenteral, and transcutaneous delivery; condoms with spermicide, diaphragm with spermicide, surgical sterilization, intrauterine device, abstinence, and post-menopause)

1. Currently breast-feeding (if female).
2. Behavioral, cognitive, or psychiatric disease that in the opinion of the investigator affects the ability of the volunteer to understand and cooperate with the study protocol.
3. Laboratory evidence of liver disease (aspartate aminotransferase [AST] and/or alanine aminotransferase [ALT] greater than the upper limit of normal of the testing laboratory).
4. Laboratory evidence of renal disease (serum creatinine greater than the upper limit of normal of the testing laboratory).
5. Laboratory evidence of hematologic disease (absolute neutrophil count < 1,500/mm3; hemoglobin less than the lower limit of normal of the testing laboratory, by sex; or platelet count < 140,000/mm3).
6. Evidence of clinically significant neurologic, cardiac, pulmonary, hepatic, endocrine, rheumatologic, autoimmune, or renal disease by history, physical examination, and/or laboratory studies including urinalysis (greater than trace protein, or any glucose on urine dip will be confirmed negative prior to enrollment).
7. Other condition that in the opinion of the investigator would jeopardize the safety or rights of a volunteer participating in the trial or would render the subject unable to comply with the protocol.
8. Participation in another investigational vaccine or drug trial within 30 days of starting this study, or while this study is ongoing.
9. Volunteer has had medical, occupational, or family problems as a result of alcohol or illicit drug use during the past 12 months
10. History of a severe allergic reaction or anaphylaxis.
11. Positive ELISA and confirmatory Western blot tests for HIV-1.
12. Positive ELISA and confirmatory immunoblot tests for HCV.
13. Positive HBsAg by ELISA.
14. Known immunodeficiency syndrome.
15. Use of corticosteroids (excluding topical or nasal) or immunosuppressive drugs within 30 days of starting this study or while the study is ongoing.
16. Receipt of a live vaccine within past 4 weeks or a killed vaccine within past 2 weeks prior to entry into the study.
17. History of a surgical splenectomy.
18. Receipt of blood products within the past 6 months.
19. Previous receipt of an investigational malaria vaccine.
20. History of a known allergy to nickel.

Note: For this study, prior history of malaria or a recent visit to a malaria endemic area are not exclusion criteria.

## Treatments That Could Potentially Interfere with Vaccine-Induced Immunity

The following criteria should be checked prior to each vaccination. If any become applicable during the study, the volunteer will be excluded from receiving further doses of the study vaccine and will not be included in the immunogenicity evaluations after the time of exclusion. The volunteer will, however, be encouraged to remain in the study for further safety evaluation for doses already received.

1. Use of any investigational drug or investigational vaccine other than the study vaccine during the study period.
2. Administration of chronic (defined as more than 14 days) immunosuppressants or other immune-modifying drugs 6 months prior to vaccination. (Topical and nasal steroids are allowed.)
3. Administration of a licensed vaccine 14 days before or after each vaccination.
4. Administration of immunoglobulins and/or any blood products up to 30 days after the last dose of vaccine.

## Contraindications to Vaccination

The following criteria should be checked prior to each immunization and are contraindications to further immunization. However, the volunteer will be encouraged to remain in the study for safety evaluation for doses already received. Should a female volunteer become pregnant during the course of the study, she will be referred to an appropriate specialist and followed for the duration of the pregnancy.

1. Hypersensitivity reaction following administration of the study vaccine.
2. Pregnancy, as determined by a positive urine ß-hCG.

## Indications for Deferral of Vaccination

The following AEs constitute grounds for deferral of vaccine administration at that point in time; if any one of these AEs occurs at the time scheduled for vaccination, the volunteer may be vaccinated at a later date, within the allowable time interval specified in the protocol, or withdrawn at the discretion of the investigator. The volunteer must be followed until resolution of the event as with any AE. If the volunteer is withdrawn from the study, he/she will be encouraged to continue in the safety evaluation for the duration of the study.

1. Oral temperature > 37.5°C at the time of vaccination will warrant deferral of immunization until fever and symptoms resolve.
2. Any other condition that in the opinion of the investigator poses a threat to the individual if immunized or that may complicate interpretation of the safety of the vaccine following immunization.

Such individual(s) will be followed in the clinic until the symptoms resolve or the window for immunization expires. No further vaccination will be performed if the volunteer does not recover (oral temperature  37.5°C and/or lack of symptoms) within the vaccination window described in Section 6.5 of this protocol. The volunteer, however, will be followed for safety and immunogenicity. If the individual meets any of the above criteria for deferral on the day of first immunization, the investigator may elect to exclude the volunteer from further participation in the study. Eligible alternates will then be vaccinated instead.

## Subject Withdrawal Criteria

A volunteer will not be considered to have completed the trial if any of the following reasons apply. However, any volunteer who has received at least one dose of vaccine will be encouraged to remain in the study for safety evaluation for the duration of the study.

1. *Research terminated by sponsor or investigator* – applies to the situation where the entire study is terminated by the sponsor, or investigator for any reason.
2. *Withdrawal of consent* – applies to a subject who withdraws consent to participate in the study for any reason.
3. *Noncompliant with protocol* – applies to a volunteer who does not comply with protocol-specific visits or evaluations, on a consistent basis, such that adequate follow-up is not possible and the volunteer’s safety would be compromised by continuing in the trial. Additionally, this applies to a volunteer who is lost to follow-up and is not reachable by telephone or other means of communication, and therefore not able to be located. In the event that a volunteer becomes incarcerated during the course of this study, every attempt will be made to continue to monitor for safety for the duration of the study.

4*. Other* – is used when previous categories do not apply and a written explanation is required.

# Vaccine Preparation

## Supplies

Research products for this protocol will be supplied to the study site pharmacist by the Pharmaceutical Development Section (PDS), Pharmacy Department, Clinical Center, National Institutes of Health (NIH), where the vaccines were formulated and vialed. Vaccines will be transported at 2oC to 8oC from the PDS at the NIH to the study site pharmacy with a temperature recording device. Upon receipt of vaccine supplies, the study site pharmacist will ensure that the temperature was maintained between 2oC to 8oC using the temperature recording device and it’s associated computer program. The study site pharmacy will be responsible for maintaining the appropriate supply of vaccine and will request additional vaccine in writing through the IND sponsor.

PpPfs25/ISA51 and ScPvs25/ISA51 malaria vaccines are supplied as a white emulsion in single‑dose vials containing 160 µg/mL. Additionally, the placebo (PBS/ISA51) will be supplied as a white emulsion in single dose vials. Each 2.0 mL vial contains 1.0 mL emulsion, of which 0.5 mL is the intended volume to be injected. 0.5 mL of vaccine contains 0.25 mL phosphate-buffered saline and 0.25 mL Montanide® ISA51. The placebo contains 0.25 mL of PBS and 0.25 mL Montanide® ISA51. The Drug Product conforms to established requirements for sterility, safety and identity. The 5 µg and 20 µg vaccines will be prepared in the trial site pharmacy by diluting the high dose (160 µg/mL) vaccine with placebo on the day of vaccination.

## Vaccine Storage

The PpPfs25/ISA51 and ScPvs25/ISA51 malaria vaccines should be maintained at 2oC to 8oC until just prior to administration. Vaccine should NOT be frozen at any time. Single-dose vials should be stored in the upright position. Vaccine will be prepared by the trial site pharmacist, and must be used within 4 hours and kept refrigerated at 2oC to 8oC until just before use.

## Vaccine Accountability

The trial site pharmacists are responsible for maintaining an accurate inventory and accountability record of vaccine supplies for this study. Partially used vials may not be administered to other volunteers.

## Disposition of Used/Unused Supplies

After administration of a vaccine dose, the single-dose vial will be returned to the trial site pharmacy, and vials will be accounted for and stored until monitoring by the IND Sponsor. Used vials may be disposed of according to study site protocol after monitoring has been completed. Final disposition of unused vaccine supplies will be determined by the Malaria Vaccine Development Branch, NIH, in conjunction with the IND Sponsor.

# Study Procedures

The following sections provide a detailed listing of the procedures and studies to be performed in this protocol at designated time points. The total volume of blood (approximately 365 mL) to be drawn over the duration of the trial is less than volume collected when donating a single unit of blood and should not compromise the health of trial volunteers.

## Screening (Up to 60 Days Prior to Vaccination)

1. Explain the study and Informed Consent to the volunteer.
2. Ensure the subject has signed the Informed Consent and received a signed copy of the Informed Consent.
3. Explain the HIV Informed Consent and ensure the subject has signed the HIV Informed Consent.
4. Elicit a complete medical history, including menstrual and contraceptive history and/or history of surgical sterility for female subjects.
5. Administer a complete physical examination.
6. Obtain approximately 25 mL of blood for hematology, biochemistry, blood type & screen, serologic tests for viral hepatitis and HIV in all volunteers.
7. Obtain urine for urine dipstick testing, as well as urine -hCG testing in females.
8. Counsel females to avoid becoming pregnant during the study.

## Enrollment

Volunteers will respond to advertisements distributed by the clinical trial site in local newspapers and posted flyers (See **Appendix A**). A screening visit will be scheduled after an initial contact screen by clinical trial staff, consisting of background information of the trial (**Appendix B**). During this initial screening visit, the volunteer will read the consent form and be encouraged to ask questions, and then take a multiple-choice questionnaire to evaluate consent comprehension (**Appendix C**). The volunteer must answer all questions correctly prior to being eligible for enrollment. Study staff will use incorrect answers from the questionnaire to identify those areas of the informed consent form that need further review with the volunteer. This will help ensure the volunteer has sufficient understanding before the consent form is signed. The volunteer may either sign the consent form during the screening visit or return after further consideration. Seventy two volunteers will be enrolled and assigned to one of 6 vaccine groups (5 µg, 20 µg or 80 µg of PpPfs25/ISA51 or ScPvs25/ISA51). There will be 10 volunteers in each group randomized to receive vaccine and 2 volunteers in each group randomized to receive placebo. Therefore, each of the 6 groups will have 12 volunteers each.

## Randomization

Volunteers will be randomly assigned to receive test article (PpPfs25/ISA51 or ScPvs25/ISA51)vaccine or placebo. Treatment assignment will be done by random number generator. A master log of treatment assignment will be maintained in a record separate from other study records. This log will be kept in the Center for Immunization Research laboratory in the School of Public Health. It will be kept in a locked room with limited access. The volunteers will be informed of their treatment assignment at their day 556 visit.

## Immunization Procedure

Volunteers will receive two immunizations; the second immunization will be given four months after the first. Vaccine will be prepared by the trial site pharmacist, and must be used within 4 hours. Vaccine must be kept refrigerated at 2oC to 8oC until just before use. 0.5 mL will be delivered by IM injection in the deltoid muscle with a 21‑gauge needle of appropriate length after preparation of the site with alcohol. Successive vaccinations will be given in alternating arms.

## Clinical Monitoring and Evaluation

See **Appendix D** for a tabular representation of study procedures. In addition to the procedures listed below, photographs of the injection may be taken at baseline and on follow-up visits to better assess and evaluate local reactogenicity.

Study Day 0 (Day of First Vaccination)

1. Verify that Informed Consent was obtained.
2. Verify that all applicable eligibility criteria have been met.
3. Perform abbreviated history and physical exam, focusing on any acute complaints.
4. Obtain approximately 35 mL of blood for hematology, biochemistry, antibody ELISA and membrane feed assay.
5. For females, obtain a urine sample for -hCG testing. Ensure that test is negative before vaccinating; a positive test will exclude the volunteer from the trial.
6. Record vital signs (blood pressure, temperature, heart rate, and respiratory rate).
7. Administer the vaccine.
8. Observe for at least 30 minutes after vaccination to evaluate for immediate adverse reactions.
9. Education by study staff during 30-minute post-immunization wait period describing proper use of digital thermometers, injection-site reaction measurement and malaria vaccine side-effect diaries. Study staff will also discuss signs and symptoms of potential adverse events (AEs).
10. Distribute Days 0-6 diary card.

Study Day 1

1. Perform basic history and physical exam (including injection site), emphasizing examination of any acute complaints.
2. Record vital signs.

Study Day 3

1. Perform basic history and physical exam (including injection site), emphasizing examination of any acute complaints.
2. Record vital signs.
3. Obtain approximately 10 mL of blood for hematology and biochemistry tests.

Study Day 7 +/- 1

1. Perform basic history and physical exam (including injection site), emphasizing examination of any acute complaints.
2. Record vital signs.
3. Collect Days 0-6 diary card.
4. Draw approximately 3.5 mL of blood for CBC and differential
5. Distribute Days 7-13 diary card.

Study Day 14 +/- 2

1. Perform basic history and physical exam (including injection site), emphasizing examination of any acute complaints.
2. Record vital signs.
3. Obtain approximately 15 mL of blood for hematology, biochemistry, and antibody ELISA.
4. Collect Days 7-13 diary card.
5. Distribute Days 14 – 20 diary card.

Study Day 21 +/- 2

1. Perform basic history and physical exam (including injection site), emphasizing examination of any acute complaints.
2. Record vital signs.
3. Collect Days 14 – 20 diary card.

Study Day 30 +/- 7(1 month after first vaccination)

1. Perform basic history and physical exam (including injection site), emphasizing examination of any acute complaints.
2. Record vital signs.
3. Obtain approximately 5 mL of blood for antibody ELISA.

Study Day 60 +/- 7 (2 months after first vaccination)

1. Perform basic history and physical exam (including injection site), emphasizing examination of any acute complaints.
2. Record vital signs.
3. Obtain approximately 35 mL of blood for hematology biochemistry, antibody ELISA & membrane feeding assay.

Study Day 90 +/- 7 (3 months after first vaccination)

1. Perform basic history and physical exam (including injection site), emphasizing examination of any acute complaints.
2. Record vital signs.
3. Obtain approximately 5 mL of blood for antibody ELISA.

Study Day 120 +/- 7 (Day of Second Vaccination)

1. Perform basic history and physical exam (including injection site), emphasizing examination of any acute complaints.
2. Obtain approximately 35 mL of blood for hematology, biochemistry, antibody ELISA, and membrane feeding assay
3. For females, obtain a urine sample for -hCG testing. Ensure that test is negative before vaccinating; a positive test will exclude the volunteer from the trial.
4. Record vital signs (blood pressure, temperature, heart rate and respiratory rate).
5. Administer the vaccine.
6. Observe for at least 30 minutes after vaccination to evaluate for immediate adverse reactions.
7. Education by study staff during 30-minute post-immunization wait period describing proper use of digital thermometers, injection-site reaction measurement tools and patient diaries. Study staff will also discuss signs and symptoms of potential AEs.
8. Distribute Days 0-6 diary card.

Study Day 121 (1 day after Second Vaccination)

1. Perform basic history and physical exam (including injection site), emphasizing examination of any acute complaints.
2. Record vital signs.

Study Day 123 (3 days after Second Vaccination)

1. Perform basic history and physical exam (including injection site), emphasizing examination of any acute complaints.
2. Record vital signs.
3. Obtain approximately 10 mL of blood for hematology and biochemistry tests.

Study Day 127 +/- 1 (7 days after Second Vaccination)

1. Perform basic history and physical exam (including injection site), emphasizing examination of any acute complaints.
2. Record vital signs.
3. Collect Days 0-6 diary card.
4. Draw approximately 3.5 mL of blood for CBC and differential.
5. Distribute Days 7-13 diary card.

Study Day 134 +/- 2 (14 days after Second Vaccination)

1. Perform basic history and physical exam (including injection site), emphasizing examination of any acute complaints.
2. Record vital signs.
3. Obtain approximately 35 mL of blood for hematology, biochemistry, antibody ELISA and membrane feeding assay.
4. Collect Days 7-13 diary card.
5. Distribute Days 14 – 20 diary card.

Study Day 141 +/- 2 (21 days after second vaccination)

1. Perform basic history and physical exam (including injection site), emphasizing examination of any acute complaints.
2. Record vital signs.
3. Collect Days 14 – 20 diary card.

Study Day 150 +/- 4 (30 days after second vaccination)

1. Perform basic history and physical exam (including injection site), emphasizing examination of any acute complaints.
2. Record vital signs.
3. Obtain approximately 25 mL of blood for antibody ELISA and membrane feeding assay.

Study Day 180 +/- 14 (60 days after second vaccination)

1. Perform basic history and physical exam (including injection site), emphasizing examination of any acute complaints.
2. Record vital signs.
3. Obtain approximately 35 mL of blood for hematology biochemistry, antibody ELISA, and membrane-feeding assay.

Study Day 270 +/- 14 (5 months after second vaccination)

1. Perform basic history and physical exam (including injection site), emphasizing examination of any acute complaints.
2. Record vital signs.
3. Obtain approximately 25 mL of blood for antibody ELISA, and membrane feeding assay.

Study Day 360 +/- 30 (8 months after second Vaccination)

1. Perform basic history and physical exam (including injection site), emphasizing examination of any acute complaints.
2. Record vital signs.
3. Obtain approximately 35 mL of blood for hematology, biochemistry, antibody ELISA and membrane feeding assay.

Study Day 556 +/- 30 (12 months after second Vaccination)

1. Perform basic history and physical exam (including injection site), emphasizing examination of any acute complaints.
2. Record vital signs.
3. Obtain approximately 35 mL of blood for hematology, biochemistry, antibody ELISA and membrane feeding assay.

4. Volunteer is unblinded to vaccination cohort.

Should a volunteer develop a good antibody response, as defined by investigators at the MVDB, that volunteer may be asked if he/she would consider undergoing plasmapheresis. The purpose of plasmapheresis would be to collect sufficient serum to serve as a transmission blocking antibody standard for future trials. The volunteer will be asked to sign a separate consent for the procedure. The volunteer will be under no obligation to undergo plasmapheresis and his/her decision will not affect participation in this or other trials conducted at the Center for Immunization Research..

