### Serious Adverse Event (SAE)

An SAE is an AE, whether considered related to the investigational vaccine or not, meeting one of the following conditions:

1. Death during the period of protocol-defined surveillance
2. Life threatening: defined as an event that places a subject at immediate risk of death at the time of the event and does not refer to an event that hypothetically might have caused death were it more severe
3. Hospitalization during the period of protocol-defined surveillance: defined as at least an overnight stay in the hospital or emergency ward for treatment that would have been inappropriate if administered in the outpatient setting
4. Results in a congenital anomaly or birth defect
5. Results in a persistent or significant disability or incapacity: defined as a substantial disruption of the study volunteer’s ability to carry out normal life functions
6. Any other important medical event that may not result in death, be life threatening, or require hospitalization, may be considered a serious AE when, based upon appropriate medical judgment, the event may jeopardize the subject and may require medical or surgical intervention to prevent one of the outcomes listed above

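### The Day 120 pregnancy-test step removes a positive volunteer from the trial, whereas Section 4.4 withholds only the second dose and keeps her under follow-up

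*Protocol*

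**What the plan says.** Section 6.5 lists the steps of each visit. On Day 0 (step 5) and again on Day 120, the day of the second vaccination (step 3), it gives the same instruction after the urine test: staff must have a negative result before they vaccinate, and "a positive test will exclude the volunteer from the trial".

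Section 4.4 sets out the contraindications to be checked before each immunization, and a positive urine pregnancy test is one of the two. Its consequence is that no further dose is given. The section then adds that "the volunteer will be encouraged to remain in the study for safety evaluation for doses already received", and that a woman who becomes pregnant during the study is looked after as follows: "she will be referred to an appropriate specialist and followed for the duration of the pregnancy".

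Section 4.6, on withdrawal, states the general rule for dosed volunteers: "any volunteer who has received at least one dose of vaccine will be encouraged to remain in the study for safety evaluation".

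Section 7.1.2 includes among the serious adverse events one that only pregnancy follow-up can reveal: "Results in a congenital anomaly or birth defect".

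**The concern.** For one test at one visit, the protocol gives two different dispositions. The visit list says the volunteer leaves the trial; Section 4.4 says she stays for safety evaluation and her pregnancy is followed.

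Section 6.5 is the step-by-step list that clinic staff work from, so its wording could well decide what happens on the day. A woman who was negative on Day 0 and is positive on Day 120 has received one injection of vaccine or adjuvant placebo. Section 1.4.2 says the formulations had not been tested in humans before this trial, and Section 10.3 acknowledges that the risk to a fetus is unknown. If staff apply the Day 120 clause literally, her later safety visits could stop and the outcome of the pregnancy could go unrecorded. Under Section 7.5, a single serious adverse event judged at least possibly related to the vaccine meets a stopping criterion, so a missed outcome could matter to the whole trial.

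**Working it through.** The plan gives no figure to reproduce. The check compares the text and then counts visits.

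**Comparing the rules**

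| Place | Dosed yet? | Effect of a positive test or of stopping vaccination |
|---|---|---|
| Section 4.2, exclusion 1 | No | Not eligible |
| Section 6.5, Day 0, step 5 | No | Excluded from the trial |
| Section 4.4 | Before each dose, so it includes Day 120 | No further dose; encouraged to stay for safety; pregnancy followed |
| Section 6.5, Day 120, step 3 | Yes, one dose | Excluded from the trial |
| Section 4.3 (interfering treatments) | Checked before each dose | No further dose; encouraged to stay for safety |
| Section 4.6 (withdrawal) | Yes | Encouraged to stay for safety |

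The Day 0 step agrees with Section 4.2. The Day 120 step uses the same sentence after a dose has been given, and there it departs from Section 4.4, which names this test. It also departs from the approach of Sections 4.3 and 4.6. Section 4.6 is not a direct contradiction, because pregnancy is not among its listed reasons for withdrawal, but it points the same way. A sentence carried over from Day 0 is the likely explanation.

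**What is at risk per affected volunteer (visits from Appendix D)**

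- Visits after Day 120: 121, 123, 127, 134, 141, 150, 180, 270, 360, 556 = 10.
- Visits within 21 days of the second dose, which she would not receive: 121, 123, 127, 134, 141 = 5.
- Remaining visits: 10 − 5 = 5 (Days 150, 180, 270, 360, 556).
- Of these, visits with blood count and AST/ALT/creatinine: Days 180, 360 and 556 = 3. For Days 360 and 556 the Section 6.5 step reads "Obtain approximately 35 mL of blood for hematology, biochemistry, antibody ELISA and membrane feeding assay".
- Planned time after Day 120: 556 − 120 = 436 days; 436 / 556 = 78%.

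**When a birth would fall**

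The protocol gives no figure for this. Assume conception between Day 0 and Day 120 and about 38 weeks (38 × 7 = 266 days) to delivery. Birth would then fall between about Day 266 (0 + 266) and Day 386 (120 + 266). Of the five remaining visits, Days 270 and 360 lie inside that window and Day 556 lies after it. The schedule could therefore capture the outcome if she stays in it.

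**The case against.** The best defence is that the protocol elsewhere treats leaving the trial and staying in safety evaluation as compatible. Section 4.5 says that a volunteer withdrawn after a deferral is still encouraged to continue the safety evaluation, and Section 4.6 takes a similar line. On that reading, exclusion on Day 120 need not end follow-up. Section 4.4 is also the dedicated rule: its pregnancy follow-up is stated as something that will happen, and nothing in Section 6.5 cancels it. The congenital-anomaly item in Section 7.1.2 is not limited to the surveillance period, and Section 7.3 requires all serious adverse events to be reported and followed to resolution. Finally, by Day 120 the 20-day diary period and the 60-day adverse-event window used in the Section 9.1.1 sign test are complete for the first dose, so the 78% is a share of calendar time and not of first-dose safety information.

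Much of this stands as a limit on size. The Section 4.4 duty remains in force, attendance at later visits is only encouraged, and the visit counts describe complete loss of follow-up under the most literal reading. Both sections also agree that a pregnant volunteer must not be dosed.

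It does not remove the inconsistency. Section 4.5 concerns deferral for fever or other conditions, not pregnancy, and nowhere does the protocol say that exclusion from the trial means exclusion from vaccination only. Sections 4.5 and 4.6 show that dosed volunteers are meant to be kept under observation, which makes the Day 120 clause the outlier.

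**Conclusion.** The concern holds. The Day 120 clause is wrong as written: for a volunteer who has already had a dose, it contradicts Section 4.4 on the same test at the same visit. It should be corrected.

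Per affected woman, five scheduled visits, three with safety laboratory tests, are at risk over the last 436 of 556 days (78%), together with a weaker assurance that the pregnancy outcome is recorded. These are visits at risk, not certain losses.

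The number affected is not given and is likely small: there are 72 volunteers of both sexes, and women must use reliable contraception. Sample size, power and error rates are untouched.

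One limit concerns timing. The projected schedule in Section 3.1, which the protocol calls tentative, places the last second doses in September 2006, while the revision history lists dates in 2007. If second vaccinations are complete, the clause has little prospective use, and the correction would mainly settle the status of any woman already excluded under it.

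**What to change.** In Section 6.5, Study Day 120, step 3, replace the exclusion clause with wording such as: *a positive test is a contraindication to the second vaccination; the volunteer will be encouraged to continue safety follow-up, and the pregnancy will be followed as set out in Section 4.4*. Leave the Day 0 step unchanged, since exclusion is correct before any dose.

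If any woman has already been excluded under the Day 120 clause, offer her the remaining safety visits and pregnancy follow-up under Section 4.4.

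The cost is one clause in a protocol amendment. It adds no visit, test or analysis to the plan.
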